### Step 6: Programme evaluation

The sixth step of the IM framework involved outlining a protocol for assessing the efficacy of the intervention and, subsequently, its evaluation. Despite being informed by evidence-based theories and methodologies, the success of an intervention is not guaranteed immediately. Therefore, a process evaluation is crucial for determining the efficacy of an intervention design, as it helps to measure the actual impact of the intervention and the decisions made during its planning stages [48]. A process evaluation assesses whether an intervention has achieved its behavioural, environmental, and implementation outcomes, and tries to understand the reasons behind them. This practice ensures consistent quality of the intervention, validates the ongoing resource allocation, and ultimately establishes responsibility in our health-promoting endeavours [48].

Thus, the final step of the present study involved formulating a protocol for a cluster randomised controlled trial (RCT) to evaluate the effectiveness of the NAC intervention. During this cluster RCT, older adults in experimental neighbourhoods (receiving the NAC intervention) will be compared to older adults in demographically matched control neighbourhoods within the same municipality. As previously described, all neighbourhoods were randomly assigned to one of both study arms, as outlined in Fig. 3. Ethical approval for the cluster RCT (reference number: U202209546) was authorised by the central ethical review committee of the Open Universiteit (Heerlen, the Netherlands), after which practical implementation of the cluster RCT lasted from February to December 2023. Additionally, the cluster RCT was registered at the ISRCTN trial registry (reference number: ISRCTN17170098). All participants provided written informed consent to participate in the study.

**Fig. 3. F3:**
[figure not shown]
A graphic representation of the NAC intervention and its randomised controlled trial.

#### Participants

Community-dwelling older adults (≥ 65 years) were eligible for participation, excluding individuals diagnosed with cognitive impairment, who had insufficient Dutch language proficiency, or who could not independently access local facilities (e.g. community centres and supermarkets). Each participant was assigned to the experimental or control group according to their place of residence. Accordingly, participants were categorised as urban or rural residents, considering the potential impact of urbanisation on their health and well-being. In the Netherlands, urban areas generally report higher rates of loneliness, unhappiness, life dissatisfaction, and mental health issues [77–79]. Nevertheless, these individuals generally benefit from better healthcare accessibility and cultural amenities than their rural counterparts [80]. Hence, understanding intervention effects associated with urbanisation is crucial for a nuanced comprehension of the intervention’s impact.

#### Design and procedure

Six months before recruitment for the cluster RCT, local stakeholders who pledged their commitment to the NAC intervention underwent several training and informative sessions. In the meantime, each municipality commenced participant recruitment by sending information letters and application forms to all older adults in the designated neighbourhoods. The application form included the option to choose the online or offline intervention and could be directly returned to the research team. Afterwards, older adults opting for the offline intervention received a mailed package with the pen-on-paper questionnaire, an informed consent form, a return envelope, and an invitation to the kick-off event. Those choosing the online intervention received login details and all additional information via email.

The NAC intervention formally began after the completion of the baseline questionnaire (T0). The kick-off event, held approximately 6 weeks after the beginning of the recruitment period, provided the attending participants with a brochure containing environmental information. For those unable to attend, these materials were sent by post at a later time. Follow-up questionnaires occurred 3 (T1) and 6 (T2) months post-enrolment. The experimental group received three tailored advice letters between the questionnaires, while the (waitlist) control group received one elaborate tailored advice after completing the final questionnaire.

The cluster RCT did not include formal stopping criteria, for the NAC intervention was non-invasive and primarily targeted behavioural and social outcomes. Hence, the risk of adverse events or negative health outcomes was deemed minimal by us researchers and the ethical review committee. Moreover, as our cluster RCT focused on evaluating the efficacy of the NAC intervention, this aspect could not be predefined as a stopping criterion. Additionally, logistical challenges were anticipated as potential real-world obstacles, providing valuable insights for the future practical implementation of the intervention in everyday settings. Therefore, rather than establishing stopping criteria, the cluster RCT emphasised close monitoring to address any unforeseen issues promptly.

#### Measurements

The cluster RCT had four primary outcome measures: physical activity behaviour, loneliness, social cohesion, and health-related quality of life (HRQOL). Physical activity was assessed using the validated ‘Short questionnaire to assess health-enhancing physical activity’ (SQUASH), which was selected for its reasonable reliability and validity compared to accelerometry [81]. Furthermore, subjective measures like the SQUASH effectively differentiate between various activities (e.g. cycling, gardening, and household activities) and, thereby, also capture low-intensity physical activities prevalent among older adults [47]. Loneliness was measured with the De Jong Gierveld 6-item Loneliness scale, known for its satisfactory psychometric properties [82]. Social cohesion was assessed using the 6-item scale from the Dutch CBS Safety monitor (‘Veiligheidsmonitor’ in Dutch) [83]. HRQOL was quantified using the EQ-5D-5L questionnaire, which is widely recognised in clinical trials and observational studies [84, 85]. Secondary outcome measures included digital activity and literacy, evaluated through a shortened version of the Dutch CBS questionnaire on digital skills and Internet usage (‘ICT-gebruik huishoudens en personen’ in Dutch) [86].

Furthermore, participants provided demographics and information on factors influencing their physical activity behaviour, such as attitude, self-efficacy and perceived social support. In the experimental group, additional questionnaire items assessed their experience with the NAC intervention regarding ease of use, satisfaction, appeal, personal significance and comprehension. Logging data were collected throughout the intervention for participants using NAC’s web-based components.

Given the hierarchical structure of the data, with measurements nested within participants and participants nested within neighbourhoods, multilevel linear regression analyses were employed. This approach allowed us to account for the potential clustering at the neighbourhood level, ensuring that the cluster RCT’s findings accurately reflect the intervention’s impact while controlling for intra-class correlation (ICC).

Lastly, the intervention was evaluated after the last measurement through one-on-one interviews with older adults and local stakeholders. Evaluation criteria included the perceived image of the NAC intervention in the neighbourhood, satisfaction with the collaborative approach, establishment of local networks, and community outreach. Notes from these interviews and field observations complemented the overall evaluation process.

#### Power calculation

Our sample size calculation was derived from prior research on the AP intervention, which indicated a 0.4 effect size after 6 months [45]. It was assumed that similar effects would be observed in older adults with low SES. Anticipating effects on social cohesion, loneliness, and HRQOL, we expect an effect size of 0.35. To accommodate the multilevel design of our cluster RCT, adjustments to the standard sample size are necessary to consider the estimated ICC. Based on prior AP trials, the ICC is estimated at 0.035. With an anticipated effect size of 0.35, power of 0.80, alpha of 0.05, and ICC of 0.035, approximately 360 participants were required. Accounting for an expected 40% dropout rate during the cluster RCT, 600 participants at baseline were deemed necessary. Distributing this number across the five municipalities involved, approximately 180 participants per city and 80 participants per village were needed.

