### Study area

Before commencing the IM roadmap, specific geographical areas were selected as focal points for developing the NAC intervention and tailoring it towards existing assets and resources. This decision was made due to the intervention’s neighbourhood-oriented focus, ensuring that it could be customised to suit distinct characteristics and requirements of different communities.

Five municipalities in the south-east of the Netherlands volunteered to participate in the current study: Bergeijk, Bladel, Eindhoven, Heerlen and Voerendaal. This varied group, comprising three rural villages (500–1000 residents/km^2^) and two urban cities (≥1500 residents/km^2^), provided a good mix in terms of urbanisation, allowing for the investigation of potential links between city life and healthy ageing. After evaluating demographics (e.g. age composition of the population), socioeconomic characteristics (e.g. educational level and household income) and health indicators (e.g. being overweight and physical activity behaviour), each municipality selected two similar neighbourhoods or districts for participation in the current study. Within each municipality, these two selected neighbourhoods were randomly assigned to a specific role within the current study. The other neighbourhood ultimately acted as a control group during the intervention evaluation, which will be explained in further detail in Step 6. Municipal authorities, local elderly associations and special interest groups were the first to be informed about each neighbourhood’s assignment, as they played a pivotal role in engaging other stakeholders and fostering an integral support network at the neighbourhood level.

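### On the stated inputs, 360 completers in ten neighbourhoods give about 50–60% power for an effect of 0.35, not 80%

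*Protocol article*

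**What the plan says.** The Power calculation section starts from earlier work on the parent intervention, "which indicated a 0.4 effect size after 6 months", and then lowers the target: "Anticipating effects on social cohesion, loneliness, and HRQOL, we expect an effect size of 0.35". On clustering it says "Based on prior AP trials, the ICC is estimated at 0.035", and it concludes: "With an anticipated effect size of 0.35, power of 0.80, alpha of 0.05, and ICC of 0.035, approximately 360 participants were required". Allowing for 40% dropout, this becomes 600 at baseline, distributed so that "approximately 180 participants per city and 80 participants per village were needed".

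The number of clusters comes from the Study area section: "Five municipalities in the south-east of the Netherlands volunteered to participate in the current study", and "each municipality selected two similar neighbourhoods or districts for participation in the current study". Randomisation is of neighbourhoods: "Within each municipality, these two selected neighbourhoods were randomly assigned to a specific role within the current study". The Measurements section places the clustering at neighbourhood level in a multilevel model. The power paragraph gives no cluster size, number of clusters, design effect, sidedness, baseline correlation or allowance for matching.

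**The concern.** The article presents 360 as the result of four listed inputs after adjustment for clustering. With ten clusters, an ICC of 0.035 inflates the sample size heavily, and 360 is only about 1.4 times the total needed with no clustering at all. That ratio looked too small for neighbourhoods averaging 36 completers.

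The stated power bears on how the results are read. If power for 0.35 SD is nearer one half than four fifths, a non-significant result on any one primary outcome is weak evidence against an effect of the size the trial was planned to find. A reader who takes 80% at face value would draw too firm a conclusion from it.

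**Working it through.** **Inputs.** Effect d = 0.35 SD, power 0.80, alpha 0.05 (taken as two-sided), ICC 0.035, 360 completers, 40% dropout (Power calculation). Clusters: 5 municipalities × 2 neighbourhoods = 10, five per arm (Study area). Mean completers per neighbourhood: m = 360/10 = 36.

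**Parts that reproduce.** Dropout: 360/0.6 = 600. Distribution: 2 × 180 + 3 × 80 = 600. Both are correct.

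**The figure of 360.** Without clustering, n per arm = 2(1.960 + 0.842)²/0.35² = 128.1, rounded up to 129, or 258 in total (260 with the t distribution).
- Implied design effect: 360/258 = 1.395.
- Implied cluster size: 1 + 0.395/0.035 ≈ 12.3.
- Implied number of clusters: 360/12.3 ≈ 29.

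Starting from 260 the answers are 1.385, 12.0 and 30. Neither matches a design with ten clusters.

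**Required number at 36 per cluster.** Design effect = 1 + (36 − 1) × 0.035 = 2.225. Then 258 × 2.225 = 574 (579 from 260), in 574/36 ≈ 16 neighbourhoods.

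**Power delivered by 360 completers in ten neighbourhoods.**
- SE = √(4 × 2.225/360) = 0.157 SD.
- 0.35/0.157 = 2.226.
- Normal approximation: Φ(2.226 − 1.960) = 0.605.
- Noncentral t with 10 − 2 = 8 df: 0.499.

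**Planned unequal sizes.** An equal split within each municipality gives 90 per city neighbourhood and 40 per village neighbourhood at baseline, so 54 and 24 completers. Weighting each neighbourhood by m/(1 + (m − 1) × 0.035) gives 18.91 and 13.30. The sum per arm is 2 × 18.91 + 3 × 13.30 = 77.7. SE = √(2/77.7) = 0.160, and power is 0.588 (normal) or 0.484 (8 df).

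**Limit with ten neighbourhoods.** As the number per neighbourhood grows, SE falls only to √(4 × 0.035/10) = 0.118. Power then tends to 0.841 (normal) or 0.736 (8 df). By the normal approximation, 80% needs N = 258 × 0.965/(1 − 258 × 0.035/10) ≈ 2,570. Depending on how the base of 258 is rounded, this runs from about 2,400 to 2,790, so no single figure should be quoted. On 8 df, 80% cannot be reached.

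**Precision delivered (equal sizes).**
- Effect detectable with 80% power: 2.80 × 0.157 = 0.44 SD (normal); 3.20 × 0.157 = 0.50 SD (8 df).
- 95% CI half-width: 1.96 × 0.157 = 0.31 SD (normal); 2.306 × 0.157 = 0.36 SD (8 df).

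**Effect of assumptions the section does not state** (power at 360 completers, d = 0.35):

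| Assumption | Normal | 8 df | 4 df (paired) |
|---|---|---|---|
| None (as stated) | 60% | 50% | 40% |
| One-sided test | 72% | 65% | – |
| Baseline correlation 0.5, all variance | 73% | 62% | – |
| Baseline correlation 0.5, individual-level variance only | 65% | 54% | – |
| Baseline correlation 0.61, all variance | 80% | 69% | – |
| Matching removes 50% of between-neighbourhood variance | 75% | 64% | 51% |
| Matching removes 70% | 82% | 71% | 58% |

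The 40% in the first row takes the loss of degrees of freedom from pairing with no gain in variance, so it is a worst case for a matched design.

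**The case against.** The strongest objection is that the calculation above is for an unadjusted, unmatched comparison at one time point, and the trial is not that. Neighbourhoods were paired within municipality, outcomes are measured at baseline, 3 and 6 months, and the model nests measurements within participants. Baseline adjustment or matching could raise the power, as the table shows. A reader might therefore infer from this point that the trial's real power is 50–60%. The documents do not support that, because they give neither the baseline correlation nor the gain from matching. Larger gains than those tabulated could even pass 80%: a baseline correlation of 0.8 acting on both variance components would give 90% on 8 df. Acting on individual-level variance alone, the same correlation gives 75% (normal) or 63% (8 df).

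Nor is there only one way to arrive near 360. A cluster size of 24, the completers expected in a village neighbourhood, gives about 357 for an effect of 0.4 two-sided, or about 365 for 0.35 one-sided. These do not rescue the sentence: it names 0.35, does not name a one-sided test, and the mean cluster size is 36.

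The article is also a condensed account, and a fuller protocol may hold the missing inputs. That excuses leaving inputs out. It does not excuse listed inputs that fail to give the stated result.

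Finally, the article nowhere says that it will use the 80% figure to interpret a null result, and its description of the trial as large-scale is not tied to power. The risk of misreading lies with readers of later papers and is not a stated intention of the sponsor.

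**Conclusion.** The stated sample size does not follow from the stated inputs and the ten-neighbourhood design. With d = 0.35, two-sided alpha 0.05, ICC 0.035 and no unstated variance reduction, 360 completers give about 60% power (normal) or 50% (8 df), and 59% or 48% with the planned sizes. At the stated cluster size, about 575 completers in about 16 neighbourhoods would be needed. With ten neighbourhoods the number is well over 2,000 by the normal approximation, and on 8 df power cannot exceed 74%.

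The conclusion is conditional on those inputs and is not a statement of the power the final analysis will have. A one-sided test alone does not reach 80%. A baseline correlation of about 0.61 on all variance, or matching that removes about 70% of the between-neighbourhood variance, reaches it by the normal approximation but not with small-sample degrees of freedom. The figures are for a single outcome and make no allowance for four primary outcomes.

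**What to change.** Replace the sentence in the Power calculation section with the delivered figures, for example: *Ten neighbourhoods averaging 36 completers, with an ICC of 0.035, give a design effect of about 2.2. For one outcome and a two-sided 5% test, 360 completers give about 60% power (50% with 8 degrees of freedom) for 0.35 SD, and 80% power for 0.44–0.50 SD. The expected 95% confidence interval half-width is 0.31–0.36 SD. A non-significant result does not exclude an effect of 0.35 SD.*

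If the calculation used a baseline correlation, a reduction from matching, a different cluster size or a one-sided test, state the value and its source, and recompute the power with ten clusters.

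The cost is wording and a less favourable stated power. The article reports that the trial ran from February to December 2023. The correction needs no extra participants and leaves the design unchanged; it matters most if made before effect papers cite the 80% figure.

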## Discussion

This paper aimed to describe the development process of the NAC intervention, a holistic and neighbourhood-oriented approach designed to promote healthy ageing among low-SES older adults. Leveraging the successful AP and AP-65 physical activity interventions [42, 45, 47, 87], NAC addresses the broader, multifaceted needs of low-SES older adults by incorporating elements such as professional support and information about local support services and resources. The NAC intervention was developed using the IM framework, ensuring a theoretically grounded and evidence-based approach [48]. This comprehensive method ensures that the intervention is closely tailored to the specific needs and circumstances of low-SES older adults, thereby enhancing its potential for success and contributing to creating holistic strategies for promoting healthy ageing in low-SES environments.

The newly developed NAC intervention introduces several strengths, making it a promising approach for promoting healthy ageing in older adults. First, it builds upon the proven effectiveness of the AP (and AP-65) physical activity intervention, ensuring a solid groundwork. Second, NAC offers online and offline components, accommodating diverse preferences and digital literacy levels. Third, the intervention’s co-creation process safeguards inclusivity and improves responsiveness to low-SES older adults’ actual needs and perspectives. Fourth, NAC is finely tuned to the specific context of each neighbourhood, acknowledging the importance of tailoring interventions to local nuances, such as the accessibility of resources and support networks. Lastly, a large-scale cluster RCT is planned to provide robust evidence of NAC’s impact on the health and well-being of older adults, collectively positioning it as a comprehensive and well-rounded intervention.

Many researchers and policy developers have recognised the importance of a holistic approach that transcends the focus on singular health aspects, advocating for interventions that incorporate physical, psychological, social, and environmental determinants of health. This paradigm shift is evident in recently developed interventions that address multiple life domains, such as the ‘Community Wise’ programme, which targets physical fitness, self-management abilities, social health, and well-being in low-SES older adults [88]. However, to our knowledge, the NAC intervention represents a pioneering effort by integrating this holistic framework with a systemic approach by actively involving local stakeholders in a collaborative response. Furthermore, a notable aspect of the NAC intervention is the inclusion of stakeholders outside the traditional realms of primary and social care [89]. By engaging diverse community-based support services such as community centres, libraries, sports clubs, and elderly associations, the NAC intervention leverages a broad network of resources and expertise. This interdisciplinary collaboration enhances the intervention’s capacity to comprehensively address the multifaceted needs of low-SES older adults.

Despite its strengths, the NAC intervention has several limitations that warrant acknowledgement. Foremost among these is the timing of its development and evaluation (September 2020 to December 2023), which coincided with the COVID-19 pandemic. This period brought unprecedented disruptions, including extensive lockdowns and strict social distancing measures, posing significant challenges to the integral approach’s design and implementation. Recruiting participants, particularly during the needs assessment phase, proved practically impossible, limiting access to a diverse and representative sample. Furthermore, data collected during the pandemic may only partially reflect the *normal* situation. Indeed, the very foundation of communal life was radically disrupted, which halted many neighbourhood activities and initiatives for older adults. This hindered our efforts to establish meaningful connections with older adults and stakeholders—an essential aspect of our co-creation process.

Another significant challenge in our study is the reliance of NAC’s success on effectively engaging low-SES older adults. This demographic is often considered a hard-to-reach target group, necessitating the involvement of local stakeholders to optimise outreach. Additionally, the NAC intervention’s reliance on written information may pose difficulties for older adults with limited (health) literacy. We therefore hope that the partial conversion to CEFR language level B1 and the use of videos (online) or images (offline) would enhance the intervention’s accessibility.

Finally, applying the IM framework offers benefits and drawbacks that warrant evaluation. On the one hand, the framework proved well suited for developing an integral neighbourhood-oriented approach, considering individual, community and societal factors in line with the intended holistic perspective [48, 67]. Moreover, the IM framework prioritised the active involvement of local stakeholders throughout its process, aiding in tailoring the intervention to the unique needs of our vulnerable target group and their environment [48, 90]. However, applying the IM framework is inherently complex and time-consuming. In this case, the needs assessment alone took 11 months to complete, partly due to the disruptions caused by the COVID-19 pandemic. Therefore, executing IM’s systematic approach with limited time and resources may pose challenges, particularly in community settings.

To summarise, the NAC intervention is an integral neighbourhood-oriented approach to support healthy ageing in older adults with a low SES. The intervention appears to be a promising strategy for targeting numerous ageing-related risk factors while simultaneously facilitating the existing procedures and structures in community care for older adults. Before the intervention can be widely implemented, the effectiveness of NAC will be evaluated in a large-scale cluster RCT, of which the results will be published in future papers. Insights of our research will provide recommendations and implementation guidelines for regional public health services and municipalities planning to employ an integral and community-based approach targeting healthy ageing. When proven effective, the NAC intervention will be put forward to national public health agencies that will actively distribute the intervention and make it accessible to a broader audience (e.g. the general public and practice organisations).
